#### Implementation and educational intervention

##### Preparatory clinic webinars

Preparatory webinars with each of the enrolled clinics and their participating HSSPs will be conducted prior to launching baseline data collection (detailed below). Two members of the research team will facilitate the webinars with the purpose of increasing engagement in project activities, addressing any process queries prior to the launch of the data collection, and supporting readiness for implementation and evaluation activities [109–111].

##### Educational intervention

Enrolled HSSPs at each of the participating clinics will undergo a course of self-directed VEGA or workshop VEGA, as outlined in phase 2. This phase will be influenced by the perspectives of our collaborating organizations, the health professions education literature, as well as findings of phase 1 and phase 2 of the RISE Project. Should a clinic pursue the self-directed option of the VEGA intervention, each participant within the clinic will be provided with VEGA login and password information, as well as instructions to complete all VEGA learning modules within a 4-week period (i.e., the intervention period). Reminders for intervention completion will be automatically generated and sent to participants every week via the Lime Survey interface until intervention completion or until the participant’s intervention period has passed. Should the workshop format of VEGA be selected, all HSSPs in each clinic will be invited to participate in a VEGA workshop (one per clinic), co-facilitated by at least two trained facilitators from the VEGA team. Following the completion of intervention and data collection activities, workshop participants will be provided the log-in information to have unrestricted access to the self-directed format of the VEGA modules.

##### Participant consultation

Tri-weekly participant consultation will be provided via Zoom by two clinician members of the research team following each clinic’s intervention period. Consultation will focus on supporting HSSP clinical application of family violence recognition and response principles detailed in the VEGA curriculum [110, 112]. Consultation sessions will be 45 min in duration, audio-recorded, and transcribed verbatim for qualitative data analysis (detailed below).

##### Quantitative data collection

Quantitative data related to acceptability and feasibility will be collected by the project’s research coordinator (RC); this will include tracking the number of clinics approached for participation, who request preparatory webinars, and who enroll. It will also involve tracking HSSPs within each clinic who (a) inquire about participation, (b) are eligible, and (c) enroll. The RC will also record the number of (d) (i) contacts needed to complete consent procedures and (ii) contacts to arrange all research assessments and the number of HSSPs that (e) complete VEGA training modules; (f) dropout following consent; (g) could not be reached for follow-up; (h) complete quantitative research assessments at each timepoint; and (i) are approached, agree, complete, and withdraw from the qualitative data collection strand.

Quantitative data regarding VEGA educational outcomes will be collected via HSSPs’ self-completion of assessments administered by email at three timepoints: 1 week before the intervention period (time 1; baseline), immediately following the completion of the intervention/intervention time period (time 2; post-intervention), and 3 months following intervention completion (or the intervention period for participants who take the full-time frame or who do not complete all of the VEGA learning modules) (time 3; 3-month follow-up). Given that this work is based within the overall emergent, multiphase, mixed method research design, we anticipate that measures capturing education outcomes will be the same as those administered in phase 2 of the RISE Project, which includes a brief assessment of socio-demographic characteristics. However, it is possible that these measures may expand or change throughout the duration of the research program. Additionally, at each timepoint, we will ask participants to report on the number of referrals made over the previous month to (i) intimate partner violence services, (ii) parenting services/interventions, (iii) child welfare services, or (vi) psychotherapy services.

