**Primary objective “C”**				
Determine the feasibility of collecting provider-level outcome data at baseline, 1-, and 3-month follow-up timepoints	Feasibility of secondary outcome data collection	Percentage of missing data on secondary outcomes at each time point; *RC tracking* Percentage of missing research assessments; *RC tracking*	**Criteria for success**: There will be less than 20% missing data at the individual and group level for each timepoint Our RC is able to generate estimates of effect and variability (with 95% confidence intervals) for the secondary outcomes	Percentages and range of missing data at the item, individual, and group level across sites for each of the secondary outcome measures and across secondary outcome measures Regression estimates and associated confidence intervals

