**Secondary objective “B”**				
Describe the change in the number of referrals made by enrolled providers over the previous month to (i) intimate partner violence services; (ii) parenting services/interventions; (iii) child welfare services; or (vi) psychotherapy services at baseline, post-intervention, and 3-month follow-up timepoints	Proof of concept/educational impact	Quantitative research assessments; *provider self-report*	**Hypothesis:** Provider self-reported referrals of patients to (i) intimate partner violence services; (ii) parenting services/interventions; (iii) child welfare services; or (vi) will be higher at all follow-up timepoints, relative to baseline	Regression analysis

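### Phase 3 referral counts at time 2 look back over a month that is mostly or wholly before or during training, so the post-intervention referral contrast is diluted toward no change

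*Protocol article*

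**What the plan says.** Table 3, secondary objective B, is to "Describe the change in the number of referrals made by enrolled providers over the previous month to" intimate partner violence, parenting, child welfare and psychotherapy services, at baseline, post-intervention and 3 months. Its hypothesis is that referrals "will be higher at all follow-up timepoints, relative to baseline".

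The Phase 3 section on quantitative data collection repeats the recall window: "at each timepoint, we will ask participants to report on the number of referrals made over the previous month to" those services. It defines three timepoints:
- Baseline is "1 week before the intervention period (time 1; baseline".
- Time 2 is "immediately following the completion of the intervention/intervention time period (time 2; post-intervention".
- Time 3 is "3 months following intervention completion", with the end of the period used for those who take the full time or do not finish.

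Under the educational intervention heading, the self-directed format allows four weeks. In the workshop format, "all HSSPs in each clinic will be invited to participate in a VEGA workshop (one per clinic"). The Phase 2 description of VEGA puts its length at about 3 hours.

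Secondary outcomes are analysed by regression with 95% confidence intervals and p-values, and are labelled exploratory. The Phase 3 design section says that effect and variability estimates can inform the sample size of a definitive trial.

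Table 3, primary objective C, names a different set of visits: "baseline, 1-, and 3-month follow-up timepoints".

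**The concern.** A count of referrals in the past month can show an effect of training only if that month includes days after the training. Time 2 is asked at the moment training ends, and no passage changes the recall window, delays the item or limits the hypothesis to 3 months. The recall window, the visit timing and the hypothesis are all stated in the article, and they do not fit together.

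Among the quantitative outcomes named in Table 3, referrals are the only count of what providers actually do; the others are knowledge and skill accuracy, preparedness and attitudes. A time 2 estimate pulled toward zero could be read as no early change in practice, or carried into planning for the definitive trial. Because the dilution depends on delivery format and completion day, pooling clinics would also mix different quantities under one label.

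**Working it through.** The plan gives no numerical figure for referrals to reproduce, so the check is calendar arithmetic.

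**Inputs from the protocol article.** Day 0 is the start of the intervention period. Baseline is on day -7. Self-directed completion falls on day c, from 0 to 28. The workshop is a single session, and recall is one month.

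**Assumptions.** A month is L = 28 or 30 days. The workshop day is day 0.

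**Reading 1: time 2 at own completion (day c).** The baseline window runs from -7 - L to -7, and the time 2 window from c - L to c.
- Days after completion: 0 for every c.
- Days from start to completion: c.
- Days before the start: L - c.
- Days shared with baseline: max(0, -7 - (c - L)) = max(0, L - 7 - c).

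| Completion day c | Before start (L=28 / 30) | Start to completion | After completion | Shared with baseline (L=28 / 30) |
|---|---|---|---|---|
| 0 (workshop) | 28 / 30 | 0 | 0 | 21 / 23 |
| 7 | 21 / 23 | 7 | 0 | 14 / 16 |
| 14 | 14 / 16 | 14 | 0 | 7 / 9 |
| 21 | 7 / 9 | 21 | 0 | 0 / 2 |
| 28 | 0 / 2 | 28 | 0 | 0 / 0 |

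For the workshop, 21/28 = 75% or 23/30 = 77% of the time 2 window repeats baseline.

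**Reading 2: time 2 on day 28 for everyone.** Days after completion are 28 - c, and none are shared with baseline.

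| Completion day c | After completion | Share of window (L=28 / 30) |
|---|---|---|
| 0 | 28 | 100% / 93% |
| 7 | 21 | 75% / 70% |
| 14 | 14 | 50% / 47% |
| 21 | 7 | 25% / 23% |
| 28 | 0 | 0% / 0% |

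**Effect on the contrast.** Suppose the daily referral rate rises by a proportion δ after completion and by fδ during training, with f between 0 and 1 (unknown). The expected relative change from baseline to time 2 is δ × (days after completion + f × days in training) / L. Under reading 1 with L = 30:
- workshop: 0
- day-14 finish: 14fδ/30 = 0.47fδ
- day-28 finish: 28fδ/30 = 0.93fδ

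Under reading 2 a day-0 finisher has nearly the full δ, and later finishers have progressively less weight on post-completion days.

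**Time 3.** Taking three months as 91 days, the window opens 91 - 30 = 61 or 91 - 28 = 63 days after completion, so all 28 to 30 days follow training.

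**Which reading fits better.** Time 3 is anchored to individual completion, with the period end as fallback, and the four-week period is described only for the self-directed format. Both favour reading 1 without settling it.

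**The case against.** Four points can fairly be made against the concern.

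- **The time 2 wording is ambiguous.** It can be read as the end of the four weeks, and the 1-month label in primary objective C may refer to that assessment. Early self-directed finishers would then have days after training. This stands: it rules out saying that nobody can have such days. It does not rescue the contrast, because exposure would then vary from 0 to 28 days by person.
- **Late self-directed finishers are not a before-versus-before comparison.** VEGA has four modules that can be spread over four weeks, and a day-28 finisher shares no days with baseline. This stands: their estimate is diluted by partial exposure, and the 75% to 77% repetition applies only to a day-0 workshop.
- **A reader might infer that the referral hypothesis cannot be tested, or must fail whatever VEGA does.** The article does not support that. It sets no joint success rule across timepoints, the objective is descriptive, and time 2 and time 3 can be estimated separately. In an uncontrolled before-and-after design, counts could also rise for reasons other than training.
- **Little hangs on the result.** The progression thresholds concern enrollment, completion, missing data and the ability to produce estimates, not the size of a referral effect. The limitations already disclaim causal claims, interviews and consultations also explore impact in practice, and the article allows measures to change. This lowers the severity but does not remove the mismatch.

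**Conclusion.** The concern holds in limited form. On the natural reading, the time 2 referral window contains no days after completion. For a day-0 workshop it lies wholly before training and repeats 21 to 23 of 28 to 30 baseline days. For self-directed users it mixes days before the start with days in training. On the end-of-period reading, days after training range from 0 to 28. Under either reading the pooled time 2 contrast is diluted toward no change, by an amount set by format and completion day, while secondary objective B expects a rise at that timepoint.

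This rests on a 28- to 30-day month and, for the workshop figures, on the workshop marking the start of the period. Severity is moderate: one timepoint of one exploratory secondary outcome is affected. The 3-month contrast and the feasibility objectives stand.

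**What to change.** 1. In Table 3, secondary objective B, restrict the referral hypothesis and effect estimate to baseline versus the 3-month follow-up.
2. Keep the time 2 referral item for data completeness and description only, labelled as covering the pre-training and training period. Dropping it would remove data that primary objective C uses to judge missingness at each timepoint. Calling it a second pre-training measure would be wrong for self-directed users.
3. Alternatively, if an early estimate is wanted, ask the referral item one month after training ends.
4. State whether time 2 is tied to each person's completion or to the end of the period, and reconcile the 1-month timepoint in primary objective C with the three timepoints in the data collection section.

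The cost is a few lines of wording and the loss of an early contrast of little value, or one short e-mailed item moved by a month.

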##### Quantitative data analysis

Given our primary focus on acceptability and feasibility, quantitative data for our primary objectives in phase 3 will be analyzed using descriptive statistics. In addition, based on our integration of sampling and recruitment recommendations in the literature [2, 3], we have proposed a priori thresholds for acceptability and feasibility as follows: the proportion of (a) primary care clinics and their HSSPs agreeing to participate will be 60% or greater; (b) enrolled HSSPs who complete all modules of the VEGA intervention will be 70% or greater; (c) missing data for each timepoint will be less than 20% at the HSSP and clinic levels; and (d) our team will be able to generate estimates of effect and variability for education outcome measures. Informed by the AIF and the broader implementation science literature, if more than one of these thresholds are not met, our team will consider revisions to our implementation and research procedures before proceeding to a definitive trial. Given our use of mixed methods, we expect that our qualitative data (outlined below) will be especially helpful for understanding how and why thresholds were or were not met and what can or should be augmented in the implementation and research procedures to bolster the possibility of future evaluation success. Secondary objectives will be addressed using regression analysis, with results being reported as estimates of effect (95% confidence interval) and associated *p*-values. Analyses will be exploratory, with no adjustments for multiple comparisons.

#### Qualitative research strand

##### Design, sampling, and recruitment

The qualitative strand of phase 3 will follow the principles of qualitative description [62, 63]. Driven by eligibility and enrollment procedures for the quantitative strand of data collection, we will use criterion-based sampling to select a sub-sample of HSSPs (*n* = 5–10, per clinic) who provided quantitative data to participate in a qualitative semi-structured interview. This sub-sample of HSSPs will be asked to complete an interview at two timepoints: (a) within 1 week of intervention completion and (b) 2 weeks following their submission of the 3-month quantitative research assessment. We will invite HSSPs who represent various genders, education levels, employment tenure, and previous training in family violence to participate in this strand of data collection. We will also recruit up to three managers, directors, or administrators (i.e., “managers/management”) from each of the enrolled clinics to participate in this strand of data collection. Management interviews will begin immediately following the intervention period for enrolled HSSPs in the same clinic. Eligibility and consent of HSSPs will have been obtained during quantitative study enrollment; consent for qualitative data collection will be verbally reconfirmed by the RC prior to qualitative data collection. Eligible managers will be those who have been working in their management role at the enrolled clinic for at least 6 months and who intend on working at the same clinic for the duration of the study.

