**Primary objective “D”**				
Explore the acceptability and feasibility of the intervention and evaluation procedures in (i) a sub-sample of providers who fully completed the VEGA intervention, as well as (ii) managers of participating primary care clinics	Acceptability of training Acceptability of research procedures Proof-of-concept/clinical impact	Narrative descriptions of perceived acceptability and burden of intervention and research activities; *qualitative interviews with providers and clinic managers* Narrative description of perceived value and impacts of intervention in practice; *qualitative interviews with providers and clinic managers.* Narrative descriptions of implementation successes and challenges; *consultation sessions with providers*	**N/A**	Directed content analysis; summative content analysis; thematic analysis

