Stage 2 sampling will occur at the individual level; full-population sampling will involve inviting all full-time and part-time HSSPs at each of the enrolled clinics to participate in the quantitative strand of our study [108]. We anticipate that this individual, convenience sampling approach will yield between 5 and 20 practitioners participating at each of the respective clinics. Eligible practitioners will be those who (a) have worked for the selected clinic for a minimum of 2 months, (b) intend on working (to the best of their knowledge) at the clinic until the end of the study, and (c) provide informed consent and are willing to complete quantitative and qualitative study procedures.

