##### Qualitative data collection

One-on-one interviews are a recommended method of data collection in applied qualitative research of interventions; they are a flexible approach that enables the gathering of an in-depth, first-hand account of a phenomenon in its given context [113]. A semi-structured interview guide consisting of 5–7 key, open-ended questions will guide data collection at each of the clinics; the guide will focus on the participants’ perception of the educational intervention and perceived impact, as well as the acceptability and burden of research, educational, and implementation support activities. HSSP and management interviews will be scheduled for between 45 and 60 min via Zoom at a time that is convenient for participants. Zoom is an externally hosted cloud-based service provided to the research team through our university. A link to Zoom’s privacy policy (https://zoom.us/privacy#_Toc44414835) will be provided to all potential participants in the consent form. Our research team will take all available precautions to reduce the risk of a privacy breach, including generating a unique Zoom link for each interview and providing a unique password for entry to each interview. In addition, each individual participant will be asked to refrain from using the video feature of Zoom, so that only the verbal content of each interview is audio-recorded for verbatim transcription. Management participants will also be asked to complete a brief, demographic information form. Qualitative interview participants will be provided a $75.00 honorarium in the form of an e-gift card at the completion of the interview.

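### The first Phase 3 provider interview is not tied to return of the time 2 assessment, so an interviewee who returns it late can discuss VEGA and its impact before answering the time 2 scales.

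*Protocol article*

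**What the plan says.** Three parts of Phase 3 bear on this.

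- **Interview timing** (Qualitative research strand, Design, sampling, and recruitment). The two provider interviews are set at "a) within 1 week of intervention completion and (b) 2 weeks following their submission of the 3-month quantitative research assessment". The first runs from the end of the intervention, the second from receipt of a questionnaire.
- **Time 2 timing and mode** (Quantitative data collection). Time 2 is placed "immediately following the completion of the intervention/intervention time period (time 2; post-intervention", and outcome data come from "self-completion of assessments administered by email at three timepoints".
- **Interview content** (Qualitative data collection). The guide covers the provider's "perception of the educational intervention and perceived impact", together with acceptability and burden, in sessions of 45 to 60 minutes.

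On who is interviewed, the qualitative strand gives "5–10, per clinic) who provided quantitative data", and Table 3 (primary objective D) gives "a sub-sample of providers who fully completed the VEGA intervention". Neither names time 2.

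**The concern.** The protocol protects the 3-month assessment from the interview by putting the interview after submission. It gives the time 2 assessment no such protection, although both interviews ask about VEGA and what it has changed.

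A provider who has just spent up to an hour talking to the research team about the programme and its effect on practice may answer differently afterwards, most plausibly on self-rated preparedness and attitudes. Three uses of time 2 would be affected:

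- The change from baseline to time 2 is one of the contrasts under secondary objective A.
- The effect and variability estimates are meant to inform the sample size of a definitive trial.
- The integrated analysis sets outcome scores beside interview excerpts on perceived value and impact. If the interview came before the score, the two sources are less independent than that display implies.

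**Working it through.** No figure in the plan needs reproducing. The check sets the timing rules side by side and then asks how much of the sample could be exposed.

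**1. Anchors**

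| Event | Runs from | Order fixed against its partner? |
|---|---|---|
| Time 2 assessment | Completion of VEGA, or end of the intervention period | No |
| Interview 1 | Completion of VEGA, within 7 days | No |
| Interview 2 | Submission of the 3-month assessment, plus 2 weeks | Yes, the assessment comes first |

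Time 2 and interview 1 share a starting point. On paper time 2 comes first, because it is due immediately and the interview has a week. In practice the order depends on when the form is returned.

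**2. Cases, counting days from completion**

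- Form returned on day 0 or 1, interview on day 4: order kept.
- Interview on day 2, form returned on day 5: order reversed, with both inside the first week.
- Form returned after day 7, interview held on schedule: order always reversed.

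**3. Do the sampling rules secure the order?**

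- Having provided quantitative data names no timepoint, so baseline data alone would qualify.
- Full completion of VEGA concerns the modules, not the time 2 form.
- The section on qualitative and integrated analyses starts qualitative work after the clinic's intervention period. A provider who finishes self-directed VEGA early may then have longer to return time 2 before any interview. For a provider who uses the whole period, both fall due together and the order stays open.

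**4. Share of the sample that could be exposed**

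Inputs: 2 clinics in each of 3 provinces, so 6 clinics; 5 to 10 interviewees per clinic; and an expectation that recruitment "will yield between 5 and 20 practitioners participating at each of the respective clinics".

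- Interviewees: 6 × 5 = 30 to 6 × 10 = 60.
- Participants: 6 × 5 = 30 to 6 × 20 = 120.
- Interviewed share of a clinic: from 5/20 = 25% to 5/5 = 100%.
- With about 40 participants in all, the number the protocol cites as generally sufficient, the share is at least 30/40 = 75%.

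These are ceilings on exposure. Only interviewees who return time 2 after the interview are affected, and the protocol gives no rate for that. If it were 10% to 30% (an assumption), the number would run from 30 × 0.10 = 3 to 60 × 0.30 = 18 providers.

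**5. Effect on the mean**

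Shift in mean time 2 change = (share interviewed) × (share of those returning after the interview) × (mean score shift from the interview). The document bounds only the first factor, so no numerical bias follows from it.

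**The case against.** The strongest reply is that time 2 is due immediately and the interview only within a week, so the intended order is already right and a reversal needs a late form. That stands, and it is why the point is a possibility. It does not close the gap: a due time is not a return time, and for time 3 the protocol did not rely on the due date but tied the interview to submission.

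A second reply is that return windows and interview logistics belong in a full protocol or study manual, which a journal article condenses. A missing window alone would indeed be no finding. The point rests on what the article does state: two interview anchors, only one of which protects its assessment.

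Third, the interview consists of a few open questions, with no teaching or feedback described, and an early interview has value for fresh recall. Both are fair. The first makes a shift in vignette accuracy or actual knowledge less likely than one in self-rated preparedness. The second limits how far the interview should be moved.

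Four stronger readings are tempting, and the document does not support them.

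- **That late responders will be interviewed first and time 2 is compromised.** Nothing shows how many forms come back late.
- **That late returns are expected because the coordinator chases forms.** The coordinator counts "contacts to arrange all research assessments". This is a feasibility tally and says nothing about repeated chasing.
- **That the bias can be put in standard deviation units.** Both the late share and the score shift would have to be assumed. A 25% interviewed share also implies 20 providers in each clinic, about 120 in all, so it cannot be set against precision at 40 participants.
- **That time 2 change is otherwise a clean measure of VEGA alone.** Consultation sessions begin after each clinic's intervention period, so a late form may follow a consultation whatever happens with the interview.

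**Conclusion.** The point holds as a minor, cheap improvement to scheduling. The stated rule for interview 1 allows the interview to come before the time 2 scales; the rule for interview 2 does not allow this at 3 months. The consequence is confined to interviewees who return time 2 late and to outcomes analysed as secondary and exploratory, in a design for which the authors already disclaim causal conclusions. The acceptability and feasibility aims of Phase 3 do not depend on it. The conclusion assumes only that some emailed forms may come back after the interview and that a conversation about impact can influence later self-ratings. Neither is quantified in the document, so no size is claimed.

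**What to change.** In Phase 3, Qualitative research strand, Design, sampling, and recruitment, time the first interview from the time 2 assessment, as is already done for the second. Hold it after time 2 is submitted or, if it is not submitted, once a fixed time 2 window (for example 7 days) closes. The fallback keeps non-submitters in the interview sample.

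Record the date of each interview and of each time 2 submission. Flag any time 2 form returned after the interview or after a consultation session, and report the time 2 change with and without the flagged forms.

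The cost is a sentence or two in the protocol, two dates per interviewee, and a delay of a few days for some first interviews. The change does not restore the order for forms returned after the window closes: those are only flagged, and the second analysis shows whether they matter.

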**Primary objective “B”**				
Determine the proportion of primary care providers who (i) enroll in the study, (ii) complete all VEGA modules, (iii) are retained for all follow-up timepoints	Acceptability and feasibility of VEGA education Acceptability and feasibility of staff recruitment and retention procedures	(i) Percentage of eligible providers that enroll; *RC tracking* (ii) Percentage of enrolled providers that complete all VEGA modules; *RC tracking* (iii) Percentage of providers that complete quantitative research assessments at all timepoints; *RC tracking*	**Criteria for success** (i) A 60% or greater enrollment rate of providers at each of the clinics; (ii) A 70% or greater VEGA completion rate among enrolled providers; (iii) 70% or more of enrolled providers will be retained at a 12-week follow-up	(i–iv) Descriptive counts, percentage, and range across provinces

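### Phase 3: the second provider interview is triggered by submitting the 3-month assessment, so interviewees who do not submit cannot help explain missing 3-month data

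*Protocol article*

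**What the plan says.** The Phase 3 qualitative strand (Protocol article, Design, sampling, and recruitment) selects 5 to 10 providers per clinic from those who gave quantitative data. Each is asked for two interviews. The first is "within 1 week of intervention completion". The second is "2 weeks following their submission of the 3-month quantitative research assessment". No other route to a second interview is described.

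On payment, the Qualitative data collection section states: "Qualitative interview participants will be provided a $75.00 honorarium in the form of an e-gift card at the completion of the interview". It does not say whether this is paid once or for each interview.

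Table 3, primary objective B, measures retention as "Percentage of providers that complete quantitative research assessments at all timepoints" and sets the criterion that "70% or more of enrolled providers will be retained at a 12-week follow-up". Primary objective C and the Quantitative data analysis section require less than 20% missing data at each timepoint. The latter section also expects the qualitative data to be "especially helpful for understanding how and why thresholds were or were not met".

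Table 3, primary objective D, describes the provider interviewees as "a sub-sample of providers who fully completed the VEGA intervention".

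**The concern.** The second interview is the only planned contact that could ask a provider, after the event, why the 3-month assessment was not completed. Making submission its trigger leaves out the providers whose answer is needed. If the 3-month missing-data threshold fails, the team would redesign its procedures for a definitive trial using accounts from responders only. If it passes, the reasons of those who were lost remain unknown.

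There is a secondary issue. Interviewees receive an additional research contact before the 3-month assessment, and submitting that assessment opens the way to the second interview, which may be paid. They may form a large part of the retention denominator, so any effect on their response would carry into the overall figure.

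**Working it through.** **1. Who can explain 3-month loss?** The relevant sources, set side by side:
- *First provider interview:* held within a week of intervention completion, about three months before the loss occurs. It can record expected burden, but not the reason for a later non-response.
- *Second provider interview:* held after the 3-month assessment, but only for those who submitted it.
- *Manager interviews:* begin straight after the intervention period, and managers are not the non-responders.
- *Consultation sessions:* run after the intervention period and are about applying VEGA in practice, not about completing research assessments.
- *Research coordinator tracking:* counts dropouts and providers who could not be reached. The listed items do not include reasons.

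None of these gives a 3-month non-responder's own account at that time.

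**2. How many accounts are at stake?** Two clinics in each of three provinces gives 2 × 3 = 6 clinics. At 5 to 10 interviewees per clinic, that is 30 to 60. Assume that non-submission among interviewees is 20% (the missing-data limit) to 30% (the loss at which the 70% retention criterion is just met):
- 20%: 0.20 × 30 = 6, to 0.20 × 60 = 12
- 30%: 0.30 × 30 = 9, to 0.30 × 60 = 18

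The true rate among interviewees is unknown. It may be lower, particularly if they are all VEGA completers.

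**3. How much of the retention denominator is interviewed?** The protocol anticipates 5 to 20 participants per clinic, so 30 to 120 enrolled.
- 5 enrolled per clinic: all interviewed, 100%
- 10 per clinic: 50% to 100%
- 20 per clinic: 5/20 = 25% to 10/20 = 50%
- about 40 in total (the reference size given in the protocol): 30/40 = 75% to 100%

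**4. What could that do to retention?** The 70% is a chosen threshold with no formula behind it, so there is no plan figure to reproduce. Let r be retention without interviews, s the interviewed share and d the uplift among interviewees. Overall retention is r + s × d, and the uplift needed to reach 70% is (0.70 − r)/s. The documents give neither r nor d; the values below are assumptions.

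| s | uplift needed, r = 65% | uplift needed, r = 60% |
|---|---|---|
| 1.00 | 5 points | 10 points |
| 0.75 | 6.7 points | 13.3 points |
| 0.50 | 10 points | 20 points |
| 0.25 | 20 points | 40 points |

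With r = 65% and d = 10 points:
- 40 enrolled, 30 interviewed: 65 + 0.75 × 10 = 72.5%. The exact binomial chance of observing at least 70% rises from 0.31 to 0.71.
- 120 enrolled, 30 interviewed: 65 + 0.25 × 10 = 67.5%. The chance rises from 0.15 to 0.32.

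The result depends strongly on the share and on an uplift that nobody has measured. It shows sensitivity, not bias.

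**The case against.** The strongest defence of the timing is that the plan relies on its qualitative data as a whole. Providers later lost may already have given a first interview that covers research burden, and most of the listed thresholds (clinic and provider enrolment, VEGA completion, ability to produce estimates) do not depend on the second interview. That is right, and it narrows the gap to 3-month non-response. It does not close it, because missing data at each timepoint is one of the listed thresholds.

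A reader might go further and infer that the interviews inflate the 70% retention result. The documents do not support this:
- They give no effect of interview contact or payment on retention.
- The $75 is paid for the interview, not the questionnaire. If it is paid only once, it could be earned before the 3-month assessment is due.
- Any overstatement would matter for the definitive trial only if that trial had no such interviews, and the protocol does not say so.
- The 70% retention criterion stands in Table 3 but not in the list of thresholds whose failure prompts revision, so its weight in the decision is unclear.

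Nor would comparing interviewed with non-interviewed providers settle the matter. If interviewees are all VEGA completers, as Table 3 says, they would probably be better retained by selection alone. With about 40 enrolled, the non-interviewed group would number 0 to 10.

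**Conclusion.** The timing point holds on the text: as written, sub-sample providers who do not submit the 3-month assessment get no second interview, and no other planned source supplies their reasons. On assumed non-submission of 20% to 30%, that is 6 to 18 of 30 to 60 interviewees. The flaw is limited to explaining 3-month non-response. It does not affect the other thresholds, and correcting it is a cheap improvement.

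On retention, the supportable statement is that added contact and an honorarium may raise 3-month response, by an unknown amount, in a group making up 25% to 100% of enrolled providers. That is a caveat on interpretation. It does not show that the 70% criterion would be wrongly met.

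**What to change.** Date the second provider interview from the scheduled 3-month assessment, for example 2 weeks after it falls due. Invite every sub-sample provider, and pay the honorarium for completing the interview whether or not the assessment was submitted. Record submission status when the invitation goes out, so that a late submission prompted by it can be recognised.

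This stays within the planned sub-sample, whose consent is obtained at enrolment. The costs are a change of wording and some refusals from non-submitters, so their accounts will be incomplete. It does not reach providers outside the sub-sample, including VEGA non-completers if the Table 3 restriction applies.

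Optionally, show 3-month retention by interview status as a descriptive caveat, using the coordinator's existing tracking of the qualitative strand. State beside it that the groups differ by selection, that the difference is not an incentive effect, and that the 70% criterion is still judged on all enrolled providers.
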